**FIGURE 2 F2:**
[figure not shown]
Study design: staff. This figure depicts only the first two measurements. The same protocol will be carried out at the 1-year mark and right before the end of the study (approximately 2 years after the beginning).

### Participants and recruitment

The proposed study intends to recruit two distinct samples: patients and staff. The patient sample will be composed of patients admitted to vascular surgery and thoracic surgery wards for an elective (non-emergency) procedure. Beyond the type of disease for patients, patients need to be aged 18 years or above and willing to participate in the study. On the other hand, exclusion criteria include emergency patients, patients already enrolled in other studies, patients with dementia, special needs or appointed guardians, and patients allocated to an intensive step-down unit and/or regimen.

The staff sample will be composed of nursing and physiotherapy staff working on either the vascular surgery or the thoracic surgery ward. Again, only employees aged 18 years or above, who have signed a consent form, will be invited to participate in the study.

To minimize background noise while ensuring that all patients also receive standard care, the study will employ a between-within interaction design, whereby patients will be allocated either to the (1) standard care group or (2) standard care with additional robot interactions. We performed the sample size calculation in the G*Power software (31), choosing the ANOVA repeated measures with within-between interaction (2 groups, 2 measurements) as the statistical test, entering a small-to-medium effect size (*f* = 0.15), and choosing a conventional significance threshold and power (α = 0.05, 1-β = 0.80). Such calculations suggest that approximately 90 patients need to be recruited overall.

The nursing and physiotherapeutic staff will be studied with a simpler within-subjects design, whereby all consenting employees will fill out the questionnaires after a period of standard care and after the use of a socially assistive robot. As such, we performed the sample size calculation in the G*Power software, choosing the Paired-samples *t*-test as the statistical test, entering a medium effect size (*d* = 0.50), and choosing a conventional significance threshold and power (α = 0.05, 1-β = 0.80). Such calculations suggest that at least 34 nursing and physiotherapeutic employees must be recruited overall.

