As socially assistive robots can provide education without the usual restraints imposed upon human employees (e.g., the robot can effortlessly repeat the same instructions multiple times) and in a gamified manner that may facilitate motivation and learning, we expect positive effects of interactive digital assistance on patient-related outcomes. More specifically, we hypothesize that patients will exhibit higher levels of patient engagement (H1) and perceived quality of medical care (H2) after being subjected to standard care with additional gamified nursing education and general/respiratory physiotherapy (delivered by a socially assistive robot) compared to levels at the beginning of the study. Furthermore, we hypothesize that patients exposed to standard care with additional gamified nursing education and general/respiratory physiotherapy (delivered by a socially assistive robot) will experience larger improvement of patient engagement (H3) and perceived quality of medical care (H4) compared to patients exposed solely to standard care (human interaction only). Additionally, due to socially assistive robots’ potential to be involved in patient care and help with some of the work tasks, we hypothesize that employees will exhibit higher self-efficacy (H5) and experience lower workload (H6) during time periods when a socially assistive robot is deployed compared to time periods when a socially assistive robot is not deployed.

In addition to our primary hypotheses, we aim to determine the percentage of non-urgent communication taken up by the social robot (RQ1), the amount of employees’ time saved by such robot-human interactions (RQ2), and the extra time of interaction provided to patients by using a socially assistive robot (RQ3). We are also interested in how these variables (e.g., the number/percentage of AI interactions) correlate with both patient- and staff-related outcomes (RQ4). Lastly, we are also interested in patients’ user experience concerning the use of a socially assistive robot (RQ5). Answering these research questions and testing the hypotheses stated above will generate a novel and comprehensive insight into the effectiveness of using socially assistive robots in healthcare.

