### Study design

The proposed study employs a between-within interaction design with multiple iterations. Patients and employees participating in the study will be recruited in a University Clinical Centre Maribor, Slovenia. The study will be carried out in 1-week intervals, followed by a 1-week washout period between each iteration. Overall, the study will be conducted over 2 years or less if the desired sample size is reached sooner.

Patients admitted to vascular and thoracic surgery wards for an elective (non-emergency) procedure will be screened for eligibility regarding the inclusion and exclusion criteria. Eligible participants will then be informed about the study characteristics and asked to fill out an informed consent form. Those who will consent to participate in the study will participate for 3–5 days. Depending on the week (see Figure 1), participants will be allocated to the standard care group (i.e., a control group that will not interact with a socially assistive robot) or standard care group with additional robot interactions. Participants from both groups will first be informed about the study and fill out the baseline questionnaires (demographic data, engagement, and perceived quality of care). Similarly, participants from both groups will be subjected to standard nursing education and general/respiratory physiotherapy delivered by nursing and physiotherapy staff. However, the patients allocated to the standard care group with additional robot interactions will additionally be subjected to nursing education and general/respiratory physiotherapy delivered by a socially assistive robot. Moreover, they will be able to call the robot for additional assistance (not related to nursing education and physiotherapy) during the whole study period. At the end of their participation, patients from both groups will be asked to fill out the questionnaires (engagement, perceived quality of care) for the second time. Patients from both groups will also be asked to rate the education and physiotherapy they received during the study period. Moreover, patients that will interact with a socially assistive robot, will also fill out the User Experience Questionnaire (30) at the end their participation.

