**FIGURE 1 F1:**
[figure not shown]
Study design: patients.

The study will be conducted in several 1-week iterations with a washout period between them (to provide enough time for new patients to be admitted). Specifically, patients will receive standard care in week 1, followed by a washout period in week 2. Patients in week 3 will then receive standard care together with robot interactions, followed by a washout period in week 4. In week 5, patients will again receive standard care. The study procedure (for patients) is outlined in Figure 1. It is worth noting that all additional variables (e.g., number of interactions with a robot) will be collected continuously during each relevant iteration. Additionally, the instructions of all self-report questionnaires will be adapted to reflect the chosen time periods and tasks. Throughout the study, patients will be observed for signs of high distress and excluded from the study if needed.

In terms of intervention content, the nursing education will contain critical information on wound care, home care considerations, and daily care explanations. On the other hand, general and respiratory physiotherapy will consist of selected instructions and exercises that can be delivered both by a human and a robot. The AI-delivered nursing education and physiotherapy instructions will employ elements of gamification.

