#### Analyses of patient-related outcomes

The patient-related outcomes, specifically patient engagement (H1, H3) and perceived quality of care (H2, H4), will primarily be analyzed with two separate mixed-design (split-plot) analyses of variance (ANOVA), with group as the between-subjects factor (2 groups: standard care, standard care with robot interactions) and time as the within-subjects factor (2 levels: T1 and T2; see Figure 1). Significant results will be followed up with *post hoc* tests using the correction to adjust for multiple testing. All results will be accompanied by effect sizes.

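### The H3/H4 model pools two surgical wards under week-based, non-randomised allocation without a ward term; this is a confounding risk that a ward-by-time term would remove at little cost

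*Protocol article*

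**What the plan says.** All references are to the protocol article.

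- **Population** (Participants and recruitment): "The patient sample will be composed of patients admitted to vascular surgery and thoracic surgery wards for an elective (non-emergency) procedure". No target or limit for the ward mix is given.
- **Allocation** (Study design): "Depending on the week (see Figure 1), participants will be allocated to the standard care group" or to the robot group. The sequence is fixed: "patients will receive standard care in week 1, followed by a washout period in week 2", then a robot week, another washout week, and standard care again. No balancing by ward is described.
- **Hypotheses** (Introduction): robot patients "will experience larger improvement of patient engagement (H3) and perceived quality of medical care (H4) compared to patients exposed solely to standard care". H3 and H4 are therefore comparisons of change.
- **Model** (Analyses of patient-related outcomes): two mixed ANOVAs, "with group as the between-subjects factor (2 groups: standard care, standard care with robot interactions) and time as the within-subjects factor". Ward is not a factor.
- **Sample size** (Participants and recruitment): about 90 patients, "choosing the ANOVA repeated measures with within-between interaction (2 groups, 2 measurements) as the statistical test", with f = 0.15, α = 0.05 and power 0.80.
- **Limitations** (Discussion): a randomised trial may be needed, participation may be selective, and only one hospital is involved. Ward mix between arms is not mentioned.

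**The concern.** The two wards treat different diseases with different operations, so engagement or perceived quality may change differently on each of them during a 3 to 5 day stay. Randomisation would make ward mix independent of arm by design. Allocation by week does not, because the mix in each arm depends on who is admitted in which weeks.

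If robot weeks contain a larger share of the ward whose patients improve more, part of that improvement is credited to the robot. If they contain a smaller share, a real effect is partly hidden. Ward is known for every patient at admission, and the article already names the factors of the model. The question is therefore how a stated model is specified, not whether a detail was left out of a condensed text.

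**Working it through.** **1. The plan's own figure.** For the within-between interaction, λ = f² × N × m / (1 − ρ), with m = 2 measurements and 1 and N − 2 degrees of freedom. The article does not state ρ. Assuming ρ = 0.5, λ = 0.0225 × 90 × 2 / 0.5 = 8.1, and power at N = 90 is 0.804. The stated figure reproduces. It corresponds to a between-arm difference d in mean change with N/4 × d² = 0.09 N, so d = √0.36 = 0.6 SD of the change score. (At ρ = 0.3 the required N would be 126, and at ρ = 0.7 it would be 56.)

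**2. When ward matters.** Shift in the group-by-time contrast = (difference in ward share between arms) × (difference in mean change between wards). If either is zero, there is no shift. A simulation with a 1 SD ward difference in level, equal at T1 and T2, and a 65/35 ward mix (10,000 runs, 45 per arm) gave a shift of 0.001 and type I error of 4.8%.

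**3. Size for a given imbalance.** The documents give neither quantity, so both are assumed. With 45 per arm, the standard error of the contrast is √(2/45) = 0.211 SD. The error SD is taken as 1.

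| Share difference | Ward difference in change | Shift | Share of 0.6 SD | Type I error | Power if the shift opposes the effect |
|---|---|---|---|---|---|
| 10 points | 0.2 SD | 0.02 SD | 3% | 5.1% | 78% |
| 20 points | 0.5 SD | 0.10 SD | 17% | 7.6% | 65% |
| 40 points | 0.8 SD | 0.32 SD | 53% | 32% | 26% |

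The error rates in this table apply only when the imbalance is fixed at the value shown.

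**4. How likely such an imbalance is.** With an even ward split and independent admissions, the SD of the share difference is √(2 × 0.25/45) = 0.105. A 20-point gap is 0.20/0.105 = 1.9 SD, with probability about 6%. If admissions cluster by week with an assumed design effect of 2 to 3, the SD rises to 0.149 to 0.183 and the probability to about 18% to 27%.

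**5. Error rate when the imbalance is only chance.** With wards drawn at random in each arm (40,000 runs), the planned test kept type I error at about 5% for ward differences in change of 0.2, 0.5 and 0.8 SD. With a true 0.6 SD effect and a 0.5 SD ward difference, power was 78% against the planned 80%.

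**6. Precision gained by adjustment.** At an even split, the ward component of the variance is 0.25 × D², where D is the ward difference in change.
- D = 0.2: 0.01/1.01, about 1% of the error variance.
- D = 0.5: 0.0625/1.0625, about 6%.

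**7. Effect of the ward term.** With ward shares of 65% and 35%, a 0.5 SD ward difference in change and no robot effect, the planned model gave a shift of 0.15 SD and type I error of about 10%. With ward in the model the shift was about 0 and type I error about 5%.

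**8. Cost of the ward term.** The variance inflation is 1/(1 − Δ²), where Δ is the difference in ward share (even split overall). Required N is 90, 92, 94, 98 and 106 for Δ = 0, 10, 20, 30 and 40 points.

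**9. Why the three-way term must stay out.** A model with group-by-ward-by-time gives both wards equal weight. At an assumed 80/20 split (36 and 9 per arm), the variance of that contrast is 0.25 × (2/36 + 2/9) = 0.069, against 2/45 = 0.044. That is about 56% more.

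**The case against.** The strongest reply is that nothing in the article ties a ward to an arm. Standard and robot weeks alternate over as long as two years, and both wards supply patients. If admissions are independent, the imbalance is chance, and the error term of the planned test already allows for it (step 5). The typical imbalance is then about 8 points, which at a 0.5 SD ward difference shifts the contrast by about 0.04 SD. This stands: a reader might infer from the 7.6% or 10% figures that the planned test has an inflated error rate, but they hold only for an imbalance fixed in advance.

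A reader might also infer that leaving ward out contradicts the plan's own aim: "To minimize background noise while ensuring that all patients also receive standard care, the study will employ a between-within interaction design". It does not. That sentence gives the reason for the design, in which each patient has a baseline. The baseline does remove stable ward differences, and no ward adjustment is promised.

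If admissions did cluster by week, that clustering would be a problem in its own right, and a ward term would not fully repair it. This also stands.

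Finally, covariates are often left to an analysis plan, the ANOVAs are described only as the primary approach, and the lack of randomisation is acknowledged. This carries less weight. The article specifies the factors of the primary model, allocation is not randomised, and ward is a known grouping that the eligibility criteria themselves create. Adjustment chosen after results are seen would be less credible than adjustment stated now.

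**Conclusion.** The point holds as a risk. Two wards are pooled, the arm follows the week without balancing by ward, and the primary model has only group and time. H3 and H4 are confounded only if the arms differ in ward mix and the wards also differ in T1-to-T2 change. The documents give no figure for either, so they do not support saying that ward mix does bias the result.

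Under the stated assumptions (45 per arm, even ward split, ρ = 0.5), a 20-point imbalance with a 0.5 SD ward difference in change shifts the contrast by 0.10 SD, about one sixth of the planned effect. With independent admissions that imbalance is a roughly 6% event and the overall error rate stays near 5%. The benefit is then mainly precision, from about 1% to about 6% of the error variance. The protection matters more if ward mix differs systematically between robot and standard weeks, which week-based allocation does not exclude. The change is worth making because it is specific and nearly free.

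**What to change.** In Analyses of patient-related outcomes:

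- Add ward (vascular or thoracic) and ward-by-time to both patient ANOVAs, or equivalently add ward to a model for the change score.
- State that the primary model has no group-by-ward-by-time term.
- Base H3 and H4 on the ward-adjusted group-by-time effect.
- Report enrolment by ward and arm.

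The cost is a short addition to the text and one degree of freedom. If ward mix differs between arms by 10 to 20 points, required N becomes about 92 to 94 instead of 90, before any gain from removing ward variation. No new data are needed, because ward is known at admission.

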## Methods and analysis

### Socially assistive robot Pepper

The Pepper robot, developed by SoftBank Robotics, is a 120 cm tall social humanoid robot optimized for human interaction and engaging with people through conversation and a touch screen. It is capable of natural movement, navigation, speech recognition, and dialogue, and is equipped with perception modules and various sensors for multimodal interactions (e.g., microphones, infrared sensors, cameras, and sonars). These functions allow for smooth interaction that does not require any specific training. The Pepper robot also has several safety mechanisms, such as bumper sensors, that prevent it from physically harming participants (29). For the purposes of the proposed study (and other studies within the H2020 project HosmartAI), the robot was taught to understand and express gestures, facial expressions, and speech in the Slovenian cultural context and language. It was also taught to perform exercises and scenarios that are part of the intervention (see section “Study design”).

The robot was first extensively tested in a laboratory setting. After this stage, we introduced the robot to employees in both participating departments. The robot was then extensively pilot tested on-site over the period of 3 months, with significant input from the clinical staff.

Despite extensive pilot testing, Pepper will be constantly supervised throughout the study by at least one researcher, enabling us to detect failures immediately and make quick repairs if needed. In the case of more severe malfunctions, the robot will be temporarily replaced with a backup unit. Moreover, in the rare event of the second unit also malfunctioning, the study will be temporarily put on hold and participants from the interrupted iteration will be excluded from analyses. The study will continue when at least one robot is working properly again.

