### Data analysis

#### Preliminary analyses

We will use the IBM SPSS Statistics 28 program for statistical analysis. In the first step, we will clean the dataset and exclude all participants with more than 20% of missing values within any questionnaire. The remaining missing data will be analyzed to determine whether they are missing completely at random and, in case this is confirmed, replaced using the expectation-maximization algorithm. We will also perform basic psychometric analyses of the questionnaires, namely the analysis of reliability as internal consistency (coefficient α), and calculate the factor scores in accordance with the scoring instructions.

In the next step, we will perform basic descriptive analyses (means and standard deviations) and check the assumptions of the chosen statistical tests (such as the normality of the distribution assumption). This step will be followed by correlational analyses (to establish relationships between different variables) and inferential tests, whereby results with a *p*-value below 0.05 will be considered statistically significant.

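### The targets of about 90 patients and at least 34 staff are given as numbers to recruit, but they are the minimum numbers needed in the analysis, so the plan's own exclusions leave the stated 80% power unsecured, mainly for patients

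*Protocol article*

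**What the plan says.** **Targets.** For patients, Participants and recruitment describes a G*Power calculation, "choosing the ANOVA repeated measures with within-between interaction (2 groups, 2 measurements) as the statistical test", with f = 0.15, alpha 0.05 and power 0.80, and concludes: "Such calculations suggest that approximately 90 patients need to be recruited overall". For staff it uses a paired t-test with d = 0.50 and the same alpha and power, and concludes: "Such calculations suggest that at least 34 nursing and physiotherapeutic employees must be recruited overall". The Abstract repeats both figures as approximate sample sizes.

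**Exclusions.** Three rules take recruited people out:
- Preliminary analyses will "exclude all participants with more than 20% of missing values within any questionnaire".
- Socially assistive robot Pepper says that, if the backup unit also fails, "participants from the interrupted iteration will be excluded from analyses".
- Study design (text under Figure 1) says that "patients will be observed for signs of high distress and excluded from the study if needed".

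**End of the study.** Study design: "Overall, the study will be conducted over 2 years or less if the desired sample size is reached sooner".

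**Tests.** Patient outcomes are analysed by a group-by-time ANOVA on T1 and T2. Staff outcomes are analysed by a paired t-test of T1 against T2.

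**The concern.** A power calculation for a two-occasion ANOVA or a paired t-test returns the number of people who contribute both measurements to the test. The article gives that output as the number to recruit and adds nothing between the two, although its own rules remove some of those recruited. The only sample size it defines is the recruitment figure, so the early end can be read as falling due at 90 enrolled patients. On that reading the study could close with fewer analysable patients than the power statement needs. A non-significant group-by-time interaction (H3, H4) would then be harder to interpret than the stated 80% suggests. The same applies to H5 and H6 if staff numbers turn out close to the floor.

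**Working it through.** **Inputs from Participants and recruitment.** Patients: 2 groups, 2 measurements, f = 0.15. Staff: d = 0.50. Both: alpha 0.05, power 0.80.

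**Inputs assumed.** Pre-post correlation rho = 0.5 for patients, which is not stated. Of the values tried (0, 0.3, 0.5, 0.7), only 0.5 reproduces 90; the others give 178, 126 and 56. The staff test is taken as two-sided, which reproduces 34; a one-sided test would give 27. No loss rate is stated, so losses are shown as a range.

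**Step 1: reproduce the patient figure.** Noncentral F for the interaction, with lambda = N × 2 × f² / (1 − rho) and df = 1 and N − 2.
- N = 90: lambda = 90 × 2 × 0.0225 / 0.5 = 8.10; power 0.804.
- N = 88, the next lower even total: lambda = 7.92; power 0.795.

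So 90 is the smallest equal-group total that reaches 0.80.

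**Step 2: reproduce the staff figure.** Noncentral t, with ncp = d × √n and df = n − 1.
- n = 34: ncp = 0.5 × √34 = 2.915; power 0.808.
- n = 33: ncp = 0.5 × √33 = 2.872; power 0.795.

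So 34 is the smallest number of pairs that reaches 0.80. Neither figure contains a reserve.

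**Step 3: how readily the missing-data rule applies.** The main scales have 6 items (quality of care, workload), 8 (self-efficacy) and 9 (engagement). One blank stays under 20% (1/6 = 17%). Two blanks exceed it on every scale (2/6 = 33%, 2/8 = 25%, 2/9 = 22%). Expectation-maximization replacement comes after this exclusion and so does not bring these people back.

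**Step 4: power if 90 patients are recruited and some are excluded** (f = 0.15, rho = 0.5; recruitment needed = 90 / (1 − loss), rounded up).

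| Assumed loss | Analysed | lambda | Power | Recruit to keep 90 |
|---|---|---|---|---|
| 0% | 90 | 8.10 | 0.804 | 90 |
| 5% | 86 | 7.74 | 0.785 | 95 |
| 10% | 81 | 7.29 | 0.760 | 100 |
| 20% | 72 | 6.48 | 0.709 | 113 |

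**Step 5: power for staff, if about 34 consent and some pairs are lost.** 33 pairs 0.795; 32 pairs 0.782; 30 pairs 0.754. The distress rule does not apply here, since it names patients only.

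**The case against.** Several stronger readings are tempting, and the article does not support them.

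- **That exclusions are made without replacement.** The article is silent on replacement and does not forbid it. After a double robot failure it says the study resumes once a unit works, so recruitment can carry on after the one event that could remove a whole iteration.
- **That staff recruitment stops at 34.** It does not. All consenting employees are to complete the questionnaires and 34 is worded as a minimum, so it is a floor. The early-end sentence concerns patient accrual in practice, because staff are first measured at the initial deployment.
- **That the study must end at 90 enrolled.** The sentence on duration does not say whether the desired size counts enrolled or usable patients. Both readings fit.
- **That any loss at all breaks the power.** Losing one or two patients (0.799 at 89, 0.795 at 88) or one staff pair (0.795) still rounds to 0.80, and the patient target is itself approximate.
- **That early discharge or withdrawal will cost patients their T2.** The article mentions neither. T2 is completed at the end of each patient's participation.

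Two further points carry weight. The patient powers depend heavily on the unstated correlation: with 0.6, even 81 patients give 0.847, while with 0.3 the full 90 give only 0.662. A journal article may also leave an attrition allowance to the full protocol, so its absence alone would be no finding.

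What remains is in the article's own text. It attaches 80% power to numbers recruited, those numbers are the bare analytic minimum, and the same article sets rules that reduce them. The words approximately and at least permit further recruitment but do not commit to it.

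**Conclusion.** The point holds in a limited form. The sample size arithmetic is correct, but its result is attached to the wrong count. The stated 80% power is not secured once the plan's exclusions remove more than a participant or two from a sample recruited to target.

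For patients, the shortfall is about 2 percentage points at 5% loss, 4 at 10% and 10 at 20% (0.804 falling to 0.785, 0.760 and 0.709). This rests on three assumptions: a correlation of 0.5, the loss rates, and recruitment ending near 90 without making up the exclusions. For staff, the shortfall is conditional on close to 34 people consenting and some pairs being lost.

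A reader might infer that the power claim is simply false for the trial as it will run. The article does not establish that, because it gives no loss rate and leaves open both replacement and what the desired size counts. The correction is worth making, but nothing here invalidates the design.

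**What to change.** 1. In Participants and recruitment, state that 90 patients and 34 staff are analysable participants, meaning those with both T1 and T2 after the exclusions.
2. In Study design, tie the early end to the number of analysable patients, within the existing 2-year window.
3. If recruitment is to stay at 90 and 34, restate the power for the number expected in the analysis and give the assumed loss: for example, about 0.76 for patients at 10% loss (81 analysed) and about 0.75 for staff with 30 pairs. This may be the more realistic route for staff, who come from only two wards and whose test uses the first T1 and T2 round.

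Cost: the first two changes need a sentence each and may add a few active weeks within the time already planned. The third costs only a slightly less favourable stated power.
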